**Methods/design::**

This randomized control trial intends to monitor cardiorespiratory health indicators and quality of life of patients diagnosed with a coronary artery disease (CAD) at the University Hospital Brno, Czech Republic. These patients will be randomly separated into 2 groups—a regular outpatient group (ROT) and an intervention training group (ITG). Both groups undergo a 12-week rehabilitation training program. The ROT group will undergo center-based exercise trainings in the hospital and receive feedback and support directly by their coach. The ITG group will be telemonitored during exercise training in their home environment via a wrist sport tester and Internet application.

All patients will be supposed to exercise at 70% to 80% of their heart rate reserve obtained from cardiopulmonary exercise test (CPX). The primary outcome is to measure and compare physical fitness values assessed at baseline and after 12 weeks of training. Physical fitness is expressed as peak oxygen uptake assessed by the CPX test. The secondary outcomes are patients, training adherence, and their quality of life.

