## Methods

2

Participants of CR-GPS project, as a single prospective randomized controlled trial, will be the patients of University Hospital (UH) Brno, Czech Republic, above the age of 18, diagnosed with CAD (angina pectoris, myocardial infarction, patients after coronary revascularization) in the last 6 months, with left ventricular ejection fraction >45%.

All eligible patients will be recommended by physiotherapists and research assistants from UH Brno. They must be clinically stable, able to undergo CPX, understand and write in Czech, and agree to participate in this project. Due to a random separation into 2 groups, all of them must have a mobile phone and free access to Internet connection.

Patients participating in CR-GPS will be further classified by cardiologist according to following criteria:No significant cardiovascular riskNo implanted cardioverter-defibrillator or pacemakerNo residual partial coronary artery stenosis requiring revascularizationNo orthopedic or neurological disability to exerciseNo mental disadvantage making cooperation impossibleNo serious oncological disease or treatment

During CR-GPS, some health problems might occur. If physical status of any participant changes significantly, he or she will be examined by the cardiologist who might change the medication. If this health problem becomes serious, this patient will be excluded from the trial. The obtained data of such patient will be further secured but not involved in final statistical evaluation.

According to Vysoký et al's study,^[24]^ number of participants calculation will be based on the improvement of peak VO_2_ 3.2 mL/kg/min with standard deviation 4.2 mL/kg/min. We will need 56 participants to reach 80% of statistical power with significance level set at *P* < .05. We count with 10% participant loss during the trial.^[25]^

At the beginning of the trial, all participants undergo baseline assessment on cycle ergometer (Ergoline Ergoselect 100, Bitz, Germany) and cardiologist will test their physical fitness through CPX. After that, they obtain a study package containing personal data questionnaire (sex, age, weight, diagnosis, pharmacological treatment), list of trial information, and informed consent form.

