### Physical fitness

3.1

Physical fitness will be measured by individual maximal CPX test with respiratory gas analysis performed on bicycle ergometer (Ergoline Ergoselect 100) using a ramp protocol. This test consists of 8 to 12 minutes cycling at 60 to 70 rpm frequency. A 12 lead ECG and blood pressure are recorded continuously during this test. Peak VO_2_ will be determined as the mean value of the last 30 seconds of exercise. Patients will be encouraged to exercise until they reach respiratory exchange ratio ≥1.10. Oxygen consumption will be measured by Metalyzer 3b (Cortex Biophysics GmbH, Leipzig, Germany).

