### Trial status

3.5

This study respects World Medical Association Declaration of Helsinki on ethic in medical research and received approval by Ethical Committee of the UH Brno, Czech Republic. This trial inclines to SPIRIT 2013 checklist standards of reporting trials and is registered at Australian New Zealand Clinical Trial Registry with registration number: ACTRN12618001170213.

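### As section 2 is written, the baseline maximal exercise test comes before participants receive the trial information and consent form

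*Protocol article*

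**What the plan says.** Section 2 (Methods) of the protocol article describes the start of the trial in sequence. First, "At the beginning of the trial, all participants undergo baseline assessment on cycle ergometer", and in the same sentence the "cardiologist will test their physical fitness through CPX". The next sentence is: "After that, they obtain a study package containing personal data questionnaire (sex, age, weight, diagnosis, pharmacological treatment), list of trial information, and informed consent" form. The text then goes on to the sending of personal information to the research team and to 1:1 computerised randomisation.

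Three other places bear on the point:

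- **Section 3.1 (Physical fitness)** describes the test: "Physical fitness will be measured by individual maximal CPX test with respiratory gas analysis performed on bicycle ergometer".
- **Abstract, Methods/design** gives its role: "The primary outcome is to measure and compare physical fitness values assessed at baseline and after 12 weeks of training". Section 2.1.3 (Outcomes) says the same in substance.
- **Section 2, eligibility conditions**, placed before the description of the test, require that patients "understand and write in Czech, and agree to participate in this project".

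**The concern.** The wording fixes an order, and the order puts the test ahead of the documents that tell a patient what the trial is and ask for consent. Participants have coronary artery disease diagnosed in the last 6 months, and under section 3.1 they are encouraged to exercise until the respiratory exchange ratio reaches at least 1.10. If a site followed the sentence as it stands, each participant would do a demanding test for the trial before being handed the written information and the form.

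What is at stake is participant protection and a clear published procedure. No estimate, error rate or sample size depends on it.

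**Working it through.** No arithmetic applies. The check is to read the described steps in order and to look elsewhere in the article for a consent step that precedes the test.

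**1. Order of steps in section 2**

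| Step | What happens | How the text places it |
|---|---|---|
| a | Patients meet the eligibility conditions, including agreement to take part | Listed before any procedure; no timing or form given |
| b | Baseline CPX on the cycle ergometer, all participants | At the start of the trial |
| c | Package with questionnaire, trial information and consent form | Expressly after step b |
| d | Personal information goes to the research team | Described after step c |
| e | Randomisation 1:1 | Described after step d |

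The link between b and c is an explicit time marker, so it does not have to be inferred from the order of the paragraphs. Steps d and e follow naturally from c, which supports reading the whole run as chronological.

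**2. Is step b a trial procedure?** On the text, yes. It is placed within the trial and applies to all participants. The abstract makes its result the baseline value of the primary outcome. Section 3.1 describes the outcome measurement on the same ergometer model as section 2. Nothing in the article calls it a routine clinical test that would be done regardless of the trial.

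**3. Is there a consent step before b?** The only candidate is the eligibility condition in step a. It does not say when or how agreement is given, or on what information. The only written trial information that the article mentions is in the package at step c. The condition therefore neither confirms nor corrects the stated order; the two sentences are simply not reconciled.

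**4. Does the order reach the randomised comparison?** No. The package (c) precedes randomisation (e) in the described order. On that order, a patient who declines after reading the information leaves before allocation, which cannot unbalance the two groups.

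**The case against.** The strongest reply is that the article says when a package is handed over, not when a patient is first informed or when the form is signed. Agreement to take part is listed before any procedure, and those who do the test are already called participants. The package need not be the first or only source of information. The flowchart (Figure 1), which might settle the order, is not reproduced in the text available, consent pages were removed, and a journal article normally leaves the detailed consent procedure to the full protocol. The test could also be ordinary care before cardiac rehabilitation.

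Much of this stands as a limit on the claim. It cannot be said that patients are in fact tested without consent, only that the published sentence says the information and form come afterwards. It does not remove the point, because this is a stated sequence and not a missing detail. If practice differs, the sentence is wrong; if practice matches, the problem is one of substance. Routine care is possible, but the article does not say so.

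Three stronger readings are tempting and are not supported:

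- **A contradiction with the ethics statement.** Section 3.5 (Trial status) says: "This study respects World Medical Association Declaration of Helsinki on ethic in medical research and received approval by Ethical Committee" of the hospital. That is a general statement, silent on when consent is taken, and the article does not quote what the Declaration requires. A conflict cannot be shown from the document.
- **Baseline data that may not be used.** Nothing in the article bears on whether the baseline results would be usable, so this would be speculation.
- **A mismatch between those tested and those randomised.** Any trial that assesses patients before randomisation may test some who are never allocated. It has no consequence for the analysis of those who are.

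**Conclusion.** The point holds as a wrongly stated sequence. As written, a maximal test that supplies the baseline of the primary outcome precedes written trial information and the consent form, and the eligibility condition on agreement is not reconciled with that order. Read literally, it applies to all 56 planned participants.

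It has no effect on the statistical validity of the comparison, given that the package comes before randomisation as described. The conclusion rests on two assumptions: that the time marker in section 2 means what it says, and that the test is done for the trial, as the article presents it. The order may be loose drafting, and the flowchart could not be checked. The point is still worth correcting before the text is relied on, because it concerns patient protection and costs almost nothing to put right.

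**What to change.** In section 2, state that trial information is given and written consent signed before the baseline CPX, and word the eligibility condition on agreement to match. Check that the flowchart and the site procedure show the same order.

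If the CPX is instead a routine clinical test done regardless of the trial, say so, and state that consent to use its result is obtained before randomisation.

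The cost is one reordered sentence and the check of the flowchart and site procedure. If the approved protocol has the same order, the ethics committee should be notified. No extra patients, visits or data are needed.

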This study was also an important source of information about how mobile phones can be effective in modern medicine. However, it is necessary to monitor physical exercise trainings in detail to provide patient with information about required heart rate, intensity, and training duration.^[21]^ Practicability of distant monitoring has been recently proved by using smartphones, ECG sensors, and GPS device.^[22]^ The 6-week-long program decreased patients’ depression and improved walking performance and physical health related to quality of life.

Fit@Home study^[23]^ from 2017 presented positive results when using a heart rate monitor. However, it mentions great limitations, such as lack of blinding for the physician regarding patient's allocation, and some patients’ discomfort while wearing the chest strap of the heart monitor.

Nevertheless, telemedicine brings great benefits, although it needs another randomized control studies to get more statistically significant data related to this approach.

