Personal information will be sent to research team from UH Brno. They will be processed and backed up according to currently valid General Data Protection Regulations (GDPR). A total of 56 patients will be separated to ITG using a telemedicine assistance and ROT group with regular center-based CR. This separation will be random, done by a computerized allocation system applying an algorithm in proportion 1:1. Investigators will not be aware of the randomized matching sequence. The patient and care providers are not blinded to the intervention.

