#### Regular outpatient training group

2.1.2

Patients in ROT group undergo a physical exercise workout period under the direct supervision of a physiotherapist specializing in CR. The patients will exercise on cycle ergometers (GE E-Bike Basic, Boston, MA) and treadmills (Forcelink BV, Amsterdam, The Netherlands).

A training session in ROT group consists of the following:1.Part—warm up—10 minutes2.Part—aerobic phase—60 minutes cycling on ergometers and walking on treadmill (according to predefined training heart rate set at 70%–80% heart rate reserve)3.Part—cool down—10 minutes

Training period is set to 60 minutes per one session 3 times a week for 12 weeks.

A physiotherapist will monitor each patient's heart rate and blood pressure. Measured data will be recorded on the secured external hard drive. At the end of study (after 12 weeks of training) all participants will be tested again. The main variable monitored is physical fitness assessed by CPX and SF-36 questionnaire. Physiotherapist will monitor the whole study process, and give patients of both groups proper feedback with possibility to consult any problems and difficulties related to training, technical issues, and their physical condition.

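### No masking is provided for whoever conducts and reads the 12-week CPX, although the primary endpoint depends on effort and encouragement

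*Protocol article*

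**What the plan says.** **Blinding.** Section 2 (Methods) states that "The patient and care providers are not blinded to the intervention". The sentence before it reads "Investigators will not be aware of the randomized matching sequence". That concerns concealment of the randomisation sequence. Outcome assessors are not mentioned.

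**Who tests.** At the start of the trial, the "cardiologist will test their physical fitness through CPX" (section 2). In the order described, this precedes randomisation. For week 12, section 2.1.2 says only: "At the end of study (after 12 weeks of training) all participants will be tested again". No tester is named there.

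**The cardiologist's other role.** If a participant's physical status changes significantly during the trial, "he or she will be examined by the cardiologist who might change the medication" (section 2).

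**The endpoint.** Section 3.1 describes an individual maximal test on a ramp protocol with gas analysis. "Patients will be encouraged to exercise until they reach respiratory exchange ratio ≥1.10". Peak VO2 is "determined as the mean value of the last 30 seconds of exercise".

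**The limitation cited elsewhere.** Of an earlier study that used a heart rate monitor, section 1 (Background) says that "it mentions great limitations, such as lack of blinding for the physician".

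**The concern.** Peak VO2 from a maximal test depends partly on how hard and how long the patient is urged on. If the person giving the encouragement at week 12 knows whether the patient trained at home or in hospital, encouragement and the moment of stopping can differ by arm, even unintentionally. Such a difference enters the primary between-arm comparison directly, and no analysis can remove it afterwards.

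The baseline test is not at risk from this, because it comes before allocation. Concealing the randomisation sequence prevents selection at entry but does nothing at week 12.

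Patients and physiotherapists cannot be blinded in a comparison of home with hospital training, so masking the assessor is the main blinding safeguard still open. It looks feasible, because coaching and feedback belong to the physiotherapists (sections 2.1.1 and 2.1.2) and running a CPX does not require knowing the arm.

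**Working it through.** **Step 1. Reading the passages together**

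| Question | What the article gives |
|---|---|
| Are care providers blinded? | No (section 2) |
| Is the outcome assessor masked? | Not stated either way |
| Who runs the baseline CPX? | The cardiologist, before randomisation (section 2) |
| Who runs the week-12 CPX? | Not named (section 2.1.2) |
| Does the cardiologist give care in the trial? | Yes, but only if a participant's status changes significantly (section 2) |
| What ends the test? | RER ≥1.10 is the goal of encouragement; it is not given as an ending or validity rule (section 3.1) |
| How is peak VO2 read? | Fixed rule, mean of the last 30 seconds (section 3.1) |

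The averaging window is fixed relative to the end of exercise, but the end itself is not fixed. The tester's remaining influence is on when exercise stops.

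**Step 2. The plan's own figure**

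Inputs from section 2: difference 3.2, SD 4.2 mL/kg/min, power 80%, α = 0.05, allocation 1:1. The number of sides is not stated; two-sided is assumed because it reproduces the stated total.

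n per arm = 2 × (1.960 + 0.842)² × 4.2² / 3.2² = 2 × 7.85 × 17.64 / 10.24 ≈ 27.0, rounded up to 28.

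The total is 56, as stated. This supports using SD 4.2 and 28 per arm for a two-arm comparison.

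**Step 3. Illustration of what a tester effect would do**

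The documents give no size for such a bias, so the shift *b* is an assumption, shown over a range. SD 4.2 is taken to apply to the quantity compared between arms.

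SE = 4.2 × √(2/28) = 1.12 mL/kg/min.

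*No true difference.* Two-sided rejection rate = P(Z > 1.96 − b/SE) + P(Z < −1.96 − b/SE), normal approximation.

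*True difference of 3.2, bias toward the null.* Power = Φ((3.2 − b)/SE − 1.96).

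| Spurious shift b (mL/kg/min) | b/SE | False-positive rate | Power against 3.2 |
|---|---|---|---|
| 0 | 0 | 5.0% | 81.3% |
| 0.5 | 0.45 | 7.3% | 67.2% |
| 1.0 | 0.89 | 14.5% | 50.0% |

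A shift of 0.5 to 1.0 is 16% to 31% of the planning difference (0.5/3.2 and 1.0/3.2).

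**The case against.** A reader might infer that the article describes an unblinded cardiologist measuring the primary endpoint. It does not go that far, for three reasons.

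- The cardiologist is named as tester only at baseline, when no arm exists. That the same role retests at week 12 is a natural inference, but it is not stated.
- The sentence on unblinded care providers may mean the physiotherapists who deliver the training. The cardiologist's contact during the trial is conditional, and nothing shows that the cardiologist learns the arm of participants who stay well.
- No sentence says that the week-12 tester knows the allocation.

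A reader might also infer that the trial repeats the very limitation it cites. The Background does not say that the unblinded physician in that study ran the fitness test, so whether the two weaknesses are identical cannot be settled from this document.

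Other points deserve weight. The RER target, gas analysis, ramp protocol and fixed 30-second average all narrow the room for tester influence. The article condenses a fuller protocol that is not shown, and section 3.5 says the trial follows SPIRIT 2013, so the assessor's status may be set out there. The direction of any bias is also unclear: the Discussion expects significant improvement in both groups, not superiority of home training.

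These points limit the finding but do not remove it. The article does take a position on blinding and, in doing so, protects nobody at week 12. It leaves open when exercise ends, and it treats lack of physician blinding as a serious limitation in another study. Bias in either direction would distort the comparison.

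**Conclusion.** The point holds as an absent safeguard. Patients and care providers are unblinded, and nothing masks whoever conducts and reads the 12-week CPX, the test that yields an effort-dependent primary endpoint. That the tester is in fact the unblinded cardiologist is an inference and should not be reported as a statement of the plan.

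The size is unknown. The rise in false-positive rate from 5% to 7.3% to 14.5% shows what a shift of 0.5 to 1.0 mL/kg/min would do. It assumes SD 4.2, 28 per arm with no losses, a two-sided test and the normal approximation; it does not estimate what will happen. The case for change rests on the low cost of masking and on the fact that the bias cannot be repaired in the analysis.

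**What to change.** In section 2 (Methods) and section 3.1 (Physical fitness):

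1. State who conducts and who reads the week-12 CPX.
2. Keep that person unaware of allocation: identify participants to the tester by study number only, and ask them not to disclose where they trained.
3. Use the same scripted encouragement at baseline and at week 12.
4. Record every test at which the tester learned the arm.
5. Report peak RER by arm, so that readers can see whether effort differed.

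**Cost.** Protocol wording, scheduling and a short test script. No extra test is needed and the sample size is unchanged.

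**Downside.** Some participants will reveal their arm. If the cardiologist does retest, masking may not be possible for those he or she has treated during the trial; these should be recorded as unmasked. Masking the tester also leaves the patients' own knowledge of their arm untouched, which is a further reason to report peak RER.

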### Training description

2.1

#### Intervention training group

2.1.1

Each ITG patient will be lent a wrist sport tester (Polar M430, Kempele, Finland) which monitors heart rate and other training values—time, training mode, duration, and distance.

A training session in ITG group consists of the following:1.Part—warm up—10 minutes2.Part—aerobic phase—60 minutes walking or cycling (according to predefined training heart rate set at 70% to 80% heart rate reserve)3.Part—cool down—10 minutes

Training period is set to 60 minutes per one session 3 times a week for 12 weeks.

To know what to do and how to train at home, the first 2 training sessions will be controlled by a physiotherapist at the CR clinic in the hospital. Further training will take place in home conditions. Training data (heart rate a training values) will be recorded by the wrist sport tester. Each patient will be supposed to download the data to a Polar Flow web application (secured by login and password). Each patient will get his or her own login and password. Physiotherapists will have access to all patients’ accounts to be able to check the data. These data will be further backed up on a separate secured external hard drive, and later processed and evaluated by the trial investigator.

The great advantage of using this web application is a possibility to use it as a diary. Each patient and physiotherapist can view training history; they can follow the results to see whether they are improving or not. Physiotherapists have the role of coaches who check their patients via telephone once a week and give them feedback including recommendations, advice, and training motivation.

